##### 4. Sample selection / Data sources

Given the disproportionate impact of dementia on Black persons, a key focus of the proposed research is to solicit input from Black and white FCP of PLwD. As such, by design we will recruit equal numbers of Black and white FCP in all stages of the study. Clinicians will not be excluded on the basis of their race or ethnicity. Based on research indicating women account for 2/3s of care partners overall, and more among Black persons, we expect 60-70% of FCP participants will be female and 30-40% male. Given women account for about ¾s of the hospice workforce, we expect 70-80% of clinician participants will be female and 20-30% male.

## **Aim 1. Intervention Development**

*Sample:* 5 Black and 5 white FCP, 5 clinicians, 5 research/content experts.

*Inclusion Criteria.* FCP participants must be identified in the medical file as the care partner, be the care partner of a recruitment site patient that is 65 years of age or older; identified as African American, black, or white; identified as having dementia; received home hospice care for a minimum of 1 week. FCP must also be 18 years of age or older, English speaking, receive a score of 15 or higher on the one-minute animal fluency test, and provide or have provided at least 8 hours of care per week for at least 1 month.

Clinicians must be a nurse, nurse practitioner, or social worker at VNS Health who provides care to older patients with dementia.

Research/content experts will possess expertise in dementia and/or end-of-life caregiving, including researchers, academics, community partners, or clinicians.

*Exclusion Criteria.* FCP are excluded if they are: under the age of 18; do not identify as African American, black, or white; do not speak English; primary relationship to recruitment site patient is employee or paid care partner; provides fewer than 8 hours of care per week; have provided care for less than 1 month; care partner of recruitment site patient that: is under 65 years of age; does not identify as African American, black, or white; does not have cognitive impairment; resides in a nursing home or long-term care facility,

Clinicians are excluded if they do not actively provide care to older adults

Research/content experts are excluded if they do not possess expertise in dementia and/or end-of-life caregiving.

## **Aim 2. One-arm Pilot Study**

*Sample.* Training: 10 clinicians. Assessment tool: 5 clinicians, 5 Black and 5 white FCP.

*Inclusion Criteria.* Same for FCP and clinicians as Aim 1. Additionally, clinicians will be part of the hospice clinical team chosen to participate in the one-arm pilot study and FCP will be part of caseload of participating clinicians.

*Exclusion Criteria.* Same for FCP and clinicians as Aim 1.

## **Aim 3. Pilot RCT**

Sample. 24 clinicians from up to 14 hospice clinical teams and 96 Black and White FCP. Approximately 12 clinicians and 48 FCP will be randomized to the intervention. Approximately 12 clinicians and 48 FCP will be randomized to usual care. We may enroll up to 18 clinicians in each arm (36 total) to allow for attrition and some clinicians not matching with 4 caregivers to reach goal of 48 FCP in each arm.

*Inclusion Criteria.* Same for FCP and clinicians as Aim 2.

*Exclusion Criteria.* Same for FCP and clinicians as Aim 2. Additionally, clinicians and FCP are excluded if they participated in Aim 2.

We are requesting a waiver of authorization to access electronic hospice records for three purposes: 1) screening to identify potential FCP participants based on hospice patient criteria described above; 2) monitoring clinician visits during the intervention to coordinate post-clinician visit data collection; and 2) identify outcome-relevant information including discharge status, number and timing of clinician visits, and clinician assessment of FCP burden.

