**Modified Delphi Approach with User-centered Design.** After the initial prototype development of the intervention, we will use a modified Delphi approach incorporating user-centered design process to refine the intervention. We will gather two rounds of structured feedback from key stakeholders including clinicians (5), Black (5) and white (5) FCP, and content/research experts (5). Participants will be asked to comment on the clarity and relevance of training and tool content and the feasibility of suggested strategies using structured and semi-structured interview questions. We will review and compile responses, revise intervention materials based on feedback, and request additional feedback from key informants. Informant feedback will be provided in 30-60 minute follow-up telephone, video-conferenced, or in person interviews within 4 weeks of receiving intervention materials. Clinicians and FCP will be interviewed individually and recruited from VNS Health, formerly Visiting Nurse Service of New York (VNSNY), and will be compensated $50 for each round of feedback. Research/content experts will be identified based on their expertise and compensated $250. Data collected during this process is outlined in the Appendix. Further information related to recruitment, participant inclusion/exclusion criteria, and informed consent forms are detailed in other sections of the protocol.

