## **Aim 3. Pilot RCT**

The 2-armed pilot RCT will be conducted with up to 14 VNS Health clinical hospice teams, consisting of 4-8 nurses and social workers. Up to 14 teams will be randomized to receive the intervention or standard care. Clinicians and FCP will be randomized to intervention or usual care groups by clinical team using an adaptive randomization approach that strives to maintain balance between number of Black and White caregivers in each study arm. We will work with VNS Health hospice leadership to select hospice teams serving similar patient populations. Hospice clinical teams will be recruited by posting the study on the VNS Health Intranet site that lists research opportunities for clinicians, email outreach, and announcements about the study during IDT team meetings. Clinical team members will be encouraged to participate in the study as part of ongoing quality improvement research. VNS Health research study staff will generate lists of potentially eligible FCP from participating clinicians’ patient caseloads and ask clinicians to review it and identify FCP who would be appropriate for the study. VNS Health research study staff will contact the FCP by phone to inquire about their interest in participating in the study (Aim 3 telephone script). The VNS Health research study staff will be trained to answer questions about the assessment tool and the study. If the FCP is interested, the VNS Health research study staff will screen the FCP to determine eligibility. The VNS Health research study staff will obtain the FCP’s permission to share contact information for informed consent with Rutgers research study staff so that VNS Health or Rutgers study staff can mail or email the informed consent form, obtain e-consent or oral consent, call the FCP to obtain informed consent, or arrange to accompany the hospice nurse or social worker on a scheduled visit, using the method preferred by the FCP.

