## **Clinician Post-Visit Fidelity Assessment Form** (To be distributed to clinicians following a visit with an enrolled FCP)

As part of your participation in the “Enhancing Dementia Instruction in Home Hospice Care (EDITH-HC)” study, please answer the following questions.

1. Please explain the main purpose of your visit on [insert date] with [insert patient name]?
2. [Control arm only] Please choose the option that best describes your interaction with [insert enrolled FCP name].
   1. We discussed what was happening with the patient.
   2. We discussed what was bothering the family member.
   3. We discussed what was happening with the patient and what was bothering the family member.
   4. I did not speak with the family member.
   5. Other (please explain)
3. [Intervention arm only] Please choose the option that best describes your interaction with [insert enrolled FCP name].
   1. The family member completed the [assessment tool/worksheet]] with some guidance from me.
   2. The family member completed the [assessment tool/worksheet]] with a lot of prompting from me.
   3. We completed the [assessment tool/worksheet]] together, making equal contributions.
   4. I left the [assessment tool/worksheet]] with the family member to complete on their own.
   5. I used the [assessment tool/worksheet]] as a guide, but did not complete it with the family member.
   6. We discussed what was bothering the family member, but I did not use the [assessment tool/worksheet]].
   7. I met with the family member, but we did not discuss what was bothering him/her.
   8. I did not speak with the family member during the visit.
   9. Other (please explain)
4. [Intervention arm only, if 3 d-f] Why didn’t you use the [assessment tool/worksheet] with the family member?
   1. I did not know I was supposed to do this.
   2. I forgot.
   3. I didn’t have a copy with me.
   4. There was not time to use it during the visit.
   5. The family member was not open to using the [tool/worksheet].
   6. This wasn’t an appropriate visit for the [tool/worksheet] to be used
   7. Other (please explain)
5. [intervention arm only if 3 a-c] Did you have any issues using the [assessment tool/worksheet] with the family member?
   1. No
   2. Yes (please explain)
6. [Intervention arm only, if 3 a-c] What challenge or concern did the family member identify? [text box]
7. [Intervention arm only] Did you record family member burden in the electronic hospice record following your visit?
   1. Yes

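### The Aim 3 exclusion bars only Aim 2 participants, so up to five clinicians who reviewed the videos and tool in Aim 1 can still be randomised, including to usual care

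*Protocol*

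**What the plan says.** Eligibility for the RCT is set by a chain of cross-references in Protocol section 4. Aim 3 takes over the Aim 2 exclusions and adds: "Additionally, clinicians and FCP are excluded if they participated in Aim 2". The Aim 2 exclusions are in turn "Same for FCP and clinicians as Aim 1". In Aim 1 the only exclusion for clinicians is this: "Clinicians are excluded if they do not actively provide care to older adults". Taking part in Aim 1 is not a ground for exclusion anywhere in the chain.

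Aim 1 and Aim 3 draw on the same workforce. Under the modified Delphi heading in section 3, "Clinicians and FCP will be interviewed individually and recruited from VNS Health"; in section 5, "The 2-armed pilot RCT will be conducted with up to 14 VNS Health clinical hospice teams". Aim 1 exposure is described as follows: "We will gather two rounds of structured feedback from key stakeholders including clinicians (5), Black (5) and white (5) FCP". The Appendix interview guides show what that involves. In round 1 participants comment while watching each video, restate its message, and describe the purpose of the assessment tool. Round 2 returns to both the videos and the tool.

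The two post-visit fidelity forms in the Appendix use separate interaction items by arm. The control item, introduced by "Control arm only] Please choose the option that best describes your interaction with", covers whether the parties spoke and what they discussed, and ends with a free-text option. The worksheet responses appear only in the intervention-arm item.

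**The concern.** The protocol already treats earlier contact with the intervention as a reason to keep someone out of the RCT, but applies that rule to Aim 2 alone and gives no reason for the difference. Aim 1 contact is not obviously slighter: it runs over two rounds, with interviews of 30 to 60 minutes.

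Randomising by team is meant to keep clinicians with access to the training and tool apart from those without it. Aim 1 clinicians are recruited individually, first from earlier interviewees and then by email and at team meetings, so they may belong to any team. One on a usual-care team brings knowledge of the materials into that arm. That could narrow the difference in care partner burden and raise that clinician's baseline knowledge and confidence. One on an intervention team has less room to gain.

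Section 9 says the pilot is to establish preliminary efficacy and help choose the outcome for a fully powered trial, so an avoidable bias toward no difference matters even in a small study.

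**Working it through.** **1. Reproducing the plan's figures.** Inputs from section 9: σ = 9.8 (used as a standard deviation), two-sided α = 0.05, power 0.80, R = 0.9, Vif = 1 + (4 − 1) × 0.03 = 1.09, and 48 care partners per arm. Solving the protocol's formula for δ:

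δ = √[4(1 − ρ) σ² (1.960 + 0.842)² × Vif / (R × n)]

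| ρ | Stated δ | Recomputed δ | n from stated δ |
|---|---|---|---|
| 0.5 | 6.21 | 6.17 | 47.35 |
| 0.6 | 5.56 | 5.52 | 47.25 |
| 0.7 | 4.81 | 4.78 | 47.35 |

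The stated differences agree within 1%, and each n rounds up to 48. Power at the stated differences is about 0.805. None of these figures is in dispute.

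**2. How many control clinicians could be exposed.** Five clinicians take part in Aim 1. Each RCT arm has about 12 clinicians and at most 18. The RCT pool is up to 14 teams of 4 to 8 (section 5): 14 × 4 = 56 to 14 × 8 = 112. The exposed control share c is not given, so it is ranged:

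- Aim 1 clinicians enrol at the same rate as the rest of the pool: 5/112 = 4.5% to 5/56 = 8.9%, or about 0.5 to 1.1 of 12 control clinicians.
- All five enrol and split evenly: 2.5/18 = 14% to 2.5/12 = 21%.
- All five enrol and all fall among 12 controls: 5/12 = 42%.

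**3. Dilution.** Let e be the fraction of the intervention effect that an exposed control clinician passes on, also not given. Assuming care partners are spread evenly over clinicians, the observed difference is δ × (1 − c × e). For ρ = 0.5 and δ = 6.21, the standard error is √[4 × 0.5 × 9.8² × 1.09 / (0.9 × 48)] = 2.20, and power is Φ(observed difference / 2.20 − 1.96).

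| Exposed control share | Difference, e = 1 | Power, e = 1 | Difference, e = 0.5 | Power, e = 0.5 |
|---|---|---|---|---|
| 0 | 6.21 | 0.81 | 6.21 | 0.81 |
| 5/112 | 5.93 | 0.77 | 6.07 | 0.79 |
| 5/56 | 5.66 | 0.73 | 5.93 | 0.77 |
| 2.5/18 | 5.35 | 0.68 | 5.78 | 0.75 |
| 2.5/12 | 4.92 | 0.61 | 5.56 | 0.72 |
| 5/12 | 3.62 | 0.38 | 4.92 | 0.61 |

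At ρ = 0.6 and 0.7 the power values are the same to within 0.002. With e = 0 there is no loss in any row.

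**4. Care partners.** The exclusion wording omits Aim 1 care partners too. However, the note to the screening tool in section 5 admits bereaved care partners only in Aim 1 and requires a current hospice patient for Aim 3. Aim 2 also falls between the two stages. Overlap is therefore unlikely, and the point rests on clinicians.

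**The case against.** The strongest reply is that the practical effect is probably small. Aim 1 clinicians gave feedback on prototypes that were revised in Aim 1 and again after Aim 2. They were not asked to use the tool with families. Intervention clinicians get the finished training and copies of the tool, and are asked to use it at a visit and at up to three later ones. Full carry-over is thus an upper bound, and at the pool rate only about one control clinician is involved. This stands, and it sets the size of the point. It does not explain why the exclusion stops at Aim 2. People who volunteered once may also volunteer again, and team-level allocation does not guarantee an even split.

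A reader might infer from the fidelity forms that contamination would go unmeasured, so that a null result could not be interpreted. The documents do not support that:

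- The study knows who took part in Aim 1, because participants consent and study IDs link to identities.
- Knowledge and confidence are collected at baseline.
- Both control items allow free text, and the clinician form has a general comments field.
- The end-of-study surveys in the Appendix ask about tool use and are not marked for one arm, although whether controls receive them is unclear.

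Leaving the worksheet out of the control items can also be defended. Naming it after every visit would tell control participants that it exists.

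**Conclusion.** The point holds as a gap in the Aim 3 eligibility rule: clinicians who reviewed the intervention in Aim 1 may be randomised to usual care. It is a permitted route, not evidence that contamination occurred, and at most five clinicians are involved.

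A reader might take 21% or 42% as the expected share of exposed controls. Those figures need all five to enrol, and 42% also needs all five to be allocated to a control arm of 12. The protocol supports neither as an expectation. Enrolment at the pool rate, which itself assumes all 14 teams take part and all five clinicians still belong to them, gives 4.5 to 9% and a loss of about 0.3 to 0.6 points from 6.21 even at full carry-over. Fewer teams or readier volunteering would raise the share; weaker carry-over would reduce the loss. The change is worth making because it is cheap and removes an avoidable bias. The missing worksheet option on the control forms is a trade-off and does not carry the point.

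**What to change.** In section 4, under the Aim 3 exclusion criteria, extend the prior-participation exclusion so that it covers Aim 1 or Aim 2. This changes one line and loses at most five clinicians from a pool of 56 to 112. With no Aim 1 clinicians enrolled, the planned detectable differences are unaffected by this route.

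If the sponsor prefers to keep these clinicians, record Aim 1 participation at enrolment and specify a sensitivity analysis of burden, knowledge and confidence that omits them and their matched care partners. This costs one data field and one extra analysis.

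Optionally, ask control clinicians once, at the end of the study, with how many care partners they used the tool. The end-of-study clinician survey in the Appendix already contains that item, with zero as a response, so the protocol need only say that controls answer it. That would detect tool use by any route without naming the worksheet on every control post-visit form.

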##### 5. Procedures for recruiting study subjects.

## **Aim 1. Intervention Development**

In the first instance, FCP and clinicians will be recruited from the list of interview participants in a prior stage of this study who indicated as part of their consent process that they would like to be contacted to participate in providing feedback on the intervention. FCP and clinician participants in the prior stage met similar inclusion criteria as outlined here. Prior participants will be contacted by Rutgers or VNS Health study staff by telephone to ask if they are interested in participating in the study (Aim 1 prior participant telephone script)

If enough FCP cannot be recruited from this prior FCP participant pool, we will screen recruitment site electronic hospice records to identify additional potential FCP participants. Staff at VNS Health will review hospice enrollment records to identify potentially eligible individuals. Consistent with qualitative interviewing practices, we will use a purposeful sampling method to obtain information that is likely to be most useful in answering our research questions. We will work with healthcare providers at our recruitment sites to identify patients with a family care partner who is likely to be engaged with and provide information helpful to answering our research questions. We will recruit equal numbers of black and white FCP. They will contact these individuals to determine interest in participating in the study (Aim 1 new FCP participant telephone script), conduct an initial eligibility screening, and obtain their permission to share their name and contact information with Rutgers study personnel. VNS Health will screen potential participants for eligibility according to the criteria above. VNS Health will track the number of persons screened, number of eligibility determinations, and counts of correctly identifying care recipient, and reasons for ineligibility (number of hours of caregiving and cognitive impairment in the hospice patient). VNS Health will share a summary of screening efforts with Rutgers via email. This summary will not contain any additional or identifying information about screened individuals such as names or contact information. For interested individuals who are determined to be eligible, VNS Health will obtain informed consent and permission from the individual for VNS Health to share the individual’s contact information with Rutgers. VNS Health study personnel will provide Rutgers study personnel with contact information using encrypted email or secure file transfer. Rutgers study personnel will follow up with enrolled study participants for data collection purposes.

If enough VNS Health clinicians cannot be recruited from the prior clinician participant pool, clinicians will be recruited via email (Aim 1 new clinician participant email recruitment) and attendance at clinical team meetings to tell them about the study and gauge interest in participation. In email and at meetings, VNS Health clinicians will be provided with information on how to contact Rutgers study personnel if they are interested in participating.

Research/content experts will be identified through professional networks and/or based on their expertise in the area(s) of hospice care, dementia, and health disparities. They will be contacted by phone, mail, or email using publicly available contact information. Each individual will be approached in a personalized manner based on expertise and knowledge.

FCP and clinicians will be compensated $50 for each round of feedback on intervention materials, up to $100. Research/content experts will be compensated $250 for participation in both rounds of feedback.

## **Aim 2. Single-arm Pilot Study**

The single-arm pilot study will be conducted with 1-2 VNS Health clinical hospice teams, consisting of 8-12 nurses and social workers caring for patients in specific geographic regions of New York City. Clinical team members will be encouraged to participate in the study as part of ongoing quality improvement research. They will be asked to identify Black and white FCP of PLwD on their caseloads who they think would be willing and informative participants. VNS Health research study staff may also generate lists of patients on participating clinician caseloads and ask clinicians to review it and identify FCP who would be appropriate for the study and may be willing and informative participants. VNS Health research study staff will contact the FCP by phone to inquire about their interest in participating in the study (Aim 2 telephone script). The VNS Health research study staff will be trained to answer questions about the assessment tool and the study. If the FCP is interested, the VNS Health research study staff will screen the FCP to determine eligibility. The VNS Health research study staff will obtain the FCP’s permission to share contact information for informed consent with Rutgers research study staff so that VNS Health or Rutgers study staff can mail or email the informed consent form, obtain e-consent, call the FCP to obtain informed consent, or arrange to accompany the hospice nurse or social worker on a scheduled visit, using the method preferred by the FCP.

FCP and clinicians will be compensated $50 for participation in the single-arm pilot study.

## **Aim 3. Pilot RCT**

The 2-armed pilot RCT will be conducted with up to 14 VNS Health clinical hospice teams, consisting of 4-8 nurses and social workers. Up to 14 teams will be randomized to receive the intervention or standard care. Clinicians and FCP will be randomized to intervention or usual care groups by clinical team using an adaptive randomization approach that strives to maintain balance between number of Black and White caregivers in each study arm. We will work with VNS Health hospice leadership to select hospice teams serving similar patient populations. Hospice clinical teams will be recruited by posting the study on the VNS Health Intranet site that lists research opportunities for clinicians, email outreach, and announcements about the study during IDT team meetings. Clinical team members will be encouraged to participate in the study as part of ongoing quality improvement research. VNS Health research study staff will generate lists of potentially eligible FCP from participating clinicians’ patient caseloads and ask clinicians to review it and identify FCP who would be appropriate for the study. VNS Health research study staff will contact the FCP by phone to inquire about their interest in participating in the study (Aim 3 telephone script). The VNS Health research study staff will be trained to answer questions about the assessment tool and the study. If the FCP is interested, the VNS Health research study staff will screen the FCP to determine eligibility. The VNS Health research study staff will obtain the FCP’s permission to share contact information for informed consent with Rutgers research study staff so that VNS Health or Rutgers study staff can mail or email the informed consent form, obtain e-consent or oral consent, call the FCP to obtain informed consent, or arrange to accompany the hospice nurse or social worker on a scheduled visit, using the method preferred by the FCP.

Intervention and control group FCP will be compensated up to $100 for participation in the pilot RCT: $25 for each round of data collection including baseline and up to 3 follow-up visits. Intervention group clinicians will be compensated $25 for completing the training and $25 for each FCP that they work with during the study and for whom they respond to survey questions. Our goal is to match each clinician with up to 4 caregivers, but we anticipate some will be matched with more than 4 and as such, cannot state a maximum compensation amount. Control group clinicians will be compensated up to $50: $25 for completing the baseline and post-presentation assessments and $25 for completing the post-visit assessments.

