
**Intervention.** Clinicians in the intervention group will have access to the training and assessment tool. The training may be delivered as part of a team in-service or other meeting or clinicians may access it on their own time. If the latter, they will be asked to complete the modules within 2 weeks of access being granted. They will be asked to use the assessment tool with Black and white FCP of home hospice PLwD who will be enrolled in the study by research study team members. The tool will be used during regularly scheduled visits to the patient and at up to 3 subsequent visits. Clinicians will be provided with copies of the assessment tool to complete with FCP during visits. FCP will continue to receive standard home hospice care in addition to the intervention.

**Standard Care Control.** FCP in the standard care control group will receive home hospice services as usual. These FCP will complete the same measures as participants in the intervention condition on the same timeline using identical assessment procedures.

**Hypotheses.** >70% of clinicians will 1) complete the training, 2) use the tool as intended, 3) report the training and tool are useful, and 4) report satisfaction with the training and tool. Compared to usual care: *Feasibility/acceptability:* Clinicians who complete the training and use the tool (intervention group) will have greater knowledge of dementia-related challenges in EOL care and how to manage them. Those in the intervention group will report it helps them identify individual PLwD and FCP challenges and suggest appropriate management strategies. *Primary outcome:* FCP in the intervention group will report reduced FCP burden. *Exploratory outcomes:* FCP of intervention group will experience greater self-efficacy and preparedness. PLwD of intervention group clinicians will experience increased utilization of hospice interdisciplinary team (IDT) member services and lower rates of hospice disenrollment. Exploratory analyses will examine racial disparities in FCP burden and PLwD disenrollment.

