**Measurements.** All measures will be collected by study research team members via phone call or electronic survey. All participants will be assessed on the measures listed in Table 1 (see **Appendix** for more details). FCP in both arms will be compensated $25 for an initial visit followed by $25 (e.g., by ClinCard) each time they complete a follow-up survey phone call/electronic survey, up to $100. Clinicians in the intervention arm will be compensated $25 for completing the training and $25 for each FCP with whom they use the assessment tool. Our aim is to match each clinician with up to 4 caregivers, although we anticipate some will be matched with more than 4 and as such cannot state a maximum compensation amount. Clinicians in the control arm will be compensated up to $50 for completing baseline and follow up surveys assessing knowledge and confidence in addressing dementia-specific issues in end-of-life care and for completing a brief survey following routine visits with study-enrolled FCP.

[figure not shown]

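### In Aim 3, clinicians who can know their arm decide which care partners are put forward, and only intervention clinicians are paid per care partner, so team randomisation does not protect the comparison of burden from selection

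*Protocol*

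**What the plan says.** **Allocation.** Protocol Section 5 (Aim 3. Pilot RCT) makes the team the unit of randomisation: "Up to 14 teams will be randomized to receive the intervention or standard care". The method is adaptive: "Clinicians and FCP will be randomized to intervention or usual care groups by clinical team using an adaptive randomization approach". The only balancing factor named is the number of Black and White FCP.

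**Selection of FCP.** The same section has VNS Health study staff "generate lists of potentially eligible FCP from participating clinicians’ patient caseloads" and then "ask clinicians to review it and identify FCP who would be appropriate for the study". Staff telephone, screen and consent only after that step. Section 3 (Aim 3, Intervention) says that intervention clinicians will use the tool with FCP "who will be enrolled in the study by research study team members".

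**Clinician payment.** Section 3 (Aim 3, Measurements) pays intervention clinicians $25 for the training and, in dollars, "25 for each FCP with whom they use the assessment tool". Section 5 gives the second part, again in dollars, as "25 for each FCP that they work with during the study and for whom they respond to survey questions". Both sections say that no maximum can be stated. For the other arm, Section 5 says: "Control group clinicians will be compensated up to $50". Of that sum, $25 covers the knowledge assessments and $25 covers all post-visit assessments together.

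**FCP payment.** This is equal in both arms, at up to $100.

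**The concern.** Randomising teams makes the teams comparable at the moment of allocation. It does not make comparable the FCP who are chosen afterwards by someone who knows the team's arm. If clinicians in the two arms apply different ideas of who is appropriate, or put different effort into nominating, the FCP groups can differ before any effect of the intervention. Intervention clinicians are trained to look for burden, and burden on the 12-item Zarit Burden Interview (ZBI) is the primary outcome. They also have a financial reason to nominate more FCP, which control clinicians lack.

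The preliminary efficacy result is at stake. Section 9 intends it to help identify the outcome for a fully powered trial. There is a second, smaller issue. One of the two payment texts makes the per-FCP payment conditional on using the tool, and using the tool as intended is itself one of the feasibility hypotheses with a target above 70%.

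**Working it through.** **1. Can the choice follow allocation?** No sentence gives the order, so the passages have to be read together.
- Section 3 (Aim 3) makes the length of the intervention depend on when FCP enrol, so enrolment is spread over time.
- Section 3 (Intervention) speaks of FCP still to be enrolled when it describes what intervention clinicians will do.
- Section 6 (May 2024 modification) has staff go back to clinicians already in the study to ask whether they will take more FCP.

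Together these imply that at least some FCP are chosen by clinicians whose team already has its arm.

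**2. Does the clinician know the arm?** In the intervention arm, yes, because these clinicians have the videos and the tool. For control clinicians it is an inference: no blinding is described.

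**3. Payment by number of FCP (k).** Intervention: $25 + $25 × k. Control: at most $25 + $25 = $50 for any k.

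| k | Intervention | Control (maximum) |
|---|---|---|
| 1 | $50 | $50 |
| 4 | $125 | $50 |
| 6 | $175 | $50 |

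Once a control clinician has qualified for the post-visit payment, each further FCP adds $25 in the intervention arm and $0 in the control arm.

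**4. Would the trial see the selection?** The accrual row of Table 2 (Appendix) starts at the number contacted. FCP whom the clinician dropped from the list are not counted, and no split by arm is specified.

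**5. The plan's own figures.** Section 9 gives n = [4(1−ρ)σ²(Zα/2+Zβ)²/δ²] × Vif / R. Take σ = 9.8 (used as an SD), two-sided α = 0.05, power 0.80, R = 0.9, n = 48 and Vif = 1 + 3 × 0.03 = 1.09. Solving for δ gives 6.17, 5.52 and 4.78 at ρ = 0.5, 0.6 and 0.7. The plan states 6.21, 5.56 and 4.81. Those values need n of 47.3 to 47.4, which rounds up to 48, so the plan's figures reproduce.

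**6. What a selection difference would do (illustration; the sizes are assumptions).** The same formula implies a standard error of √[4(1−ρ)σ²Vif/(R × 48)] = 2.20, 1.97 and 1.71. If the intervention has no effect and selection leaves b points in the analysed contrast, the nominal 5% false-positive rate becomes:

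| b (ZBI points) | Rate over ρ = 0.5 to 0.7 |
|---|---|
| 1 | 7% to 9% |
| 2 | 15% to 22% |
| 3 | 28% to 42% |

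**7. Direction depends on the analysis.** Suppose intervention FCP start 0.3 SD higher, that is 0.3 × 9.8 = 2.94 points. Suppose also that selection acts only through measured baseline ZBI and that SDs are equal at the two times.

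| Analysis | Formula | ρ = 0.5 | ρ = 0.7 |
|---|---|---|---|
| Unadjusted change | (1−ρ) × 2.94 | 1.47 in favour of intervention | 0.88 in favour |
| Unadjusted endpoint | ρ × 2.94 | 1.47 against | 2.06 against |
| Baseline-adjusted | – | about 0 | about 0 |

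The change-score bias at ρ = 0.5 is 1.47/6.21 = 24% of the stated detectable difference. With a gap of 0.5 SD it is 0.5 × 4.90 = 2.45 points, or 39%. The opposite gap reverses every sign.

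**The case against.** The strongest reply is that the clinician's discretion is one step inside a procedure run by staff. Staff make the list, telephone, screen against fixed criteria and take consent. Teams are to be chosen to serve similar populations, FCP are paid equally and baseline ZBI is measured. All of this is true and limits the risk. None of it removes the clinician's choice of names, and baseline adjustment would not correct selection on something unmeasured, such as receptiveness.

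A second reply is that balancing Black and White FCP by team may mean that caseloads were counted before allocation. That is possible. It would not cover FCP who are enrolled later or the additional matches sought from May 2024.

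Three stronger readings are tempting, and the documents do not support them:
- **That the bias favours the intervention by a known amount.** Section 9 mentions changes from baseline, a mixed model and a power calculation on endpoint means. These respond differently to the same baseline gap, as step 7 shows, and the gap itself is assumed. If clinicians chose FCP whose burden is stably high, change scores need not regress at all.
- **That every choice is made after allocation by clinicians who all know their arm.** The order is implied for some FCP only, and control clinicians' knowledge is inferred from the absence of blinding.
- **That payment inflates the feasibility result.** Section 3 pays once per FCP with whom the tool is used, so repeat use earns nothing more, and FCP report tool use separately. The payment rewards having more FCP. Nothing in the text links it to choosing more burdened ones.

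**Conclusion.** The concern holds as a weakness of the design. Clinicians who can know their arm narrow the list without a stated criterion, and only one arm has an uncapped payment per FCP. Team randomisation does not prevent the selection bias in FCP burden that this allows, and the planned accrual counts would not reveal it.

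The payment difference is explicit: $125 against at most $50 at four FCP. That some choices follow allocation is a deduction from rolling enrolment. The direction and size of any bias are unknown. The false-positive rates and point shifts above show sensitivity under assumed gaps and do not estimate what will happen.

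The two descriptions of what earns the per-FCP payment also differ and need to be reconciled. For a pilot this is a change that should be made, because it is cheap and the efficacy signal is meant to inform a later trial.

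**What to change.** 1. **Approach.** Study staff approach all listed potentially eligible FCP in a fixed or random order, separately for Black and White FCP. The call script should not reveal the arm. This needs care because callers are trained to answer questions about the tool.
2. **Veto.** Clinicians may remove a name only for a prespecified reason, which is recorded. A clinician who knows the arm could still veto selectively, so the reasons should be reported too.
3. **Reporting.** Extend Table 2 to give listed, vetoed, contacted and enrolled FCP by arm.
4. **Payment.** Pay clinicians in both arms the same amount once per FCP with completed post-visit surveys. Reconcile Section 3 (payment for using the tool) with Section 5 (payment for survey response), so that payment does not depend on tool use.

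**Cost.** In the control arm, 48 × $25 = $1,200. This replaces the post-visit $25 already planned for 12 to 18 clinicians (12 × $25 = $300; 18 × $25 = $450), so the net cost is about $900 to $750. The figure holds for one payment per FCP. Paying $25 for each of three post-visit surveys would cost 48 × 3 × $25 = $3,600 in the control arm alone, before that offset. Staff already make the lists and calls, so the remaining cost is a short amendment and some loss of clinician discretion. No sample-size figure changes.
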